### Sample size

Power calculations are based on the primary outcome measurement PACIC. The PACIC comprises 27 questions with an answering scale from 1 to 5. A previous unreported study showed that its standard deviation was 1.0. To detect a difference of 0.3 points with a standard deviation of 1 (a relatively small effect), with alpha = 0.05 and beta = 0.20, ICC = 0.05, a total of 51 practices with 10 patients each would be required, or 59 practices with 8 patients.

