## Background

Chronic heart failure (CHF) is a highly prevalent chronic disease with high morbidity and mortality rates. The prevalence of CHF in the Western world is 1% to 2% in the general population and at least 10% among the age group of 85 years and older [1,2]. Mortality in CHF patients is high compared to their age group [2,3]. High morbidity is associated with high hospital admission rates and reduced quality of life [4]. There are effective, evidence-based treatments which improve mortality and morbidity but use of and adherence of treatments is suboptimal despite clinical guidelines [5-9].

A large group of patients with CHF receive treatment in primary care. There are many programmes for the management of long-term conditions in primary care -- *e.g*., diabetes, COPD and depression -- but at present not for CHF, though several disease management programmes exist for CHF related to outpatient clinics. As a substantial proportion of CHF patients do not attend such clinics but visit their GP instead, these patients are not enrolled in a structured care programme.

To improve the management of CHF in primary care, we have developed an implementation programme, comprising both educational and organisational components, the latter aimed at improved and structured care. We pilot tested this programme in 19 general practices [10]. The pilot programme was targeted at implementing the prevailing practice guideline for general practice [11]. In the mean time, in the Netherlands an interdisciplinary guideline on CHF, based on the European Society of Cardiology (ESC) guideline, was developed and published in May 2010 [12]. So, we adapted the implementation programme according to this new guideline, taking into account the lessons learned in the pilot study.

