### Participants

The study population will consist of 60 general practitioners (GPs) and the CHF patients they will include. GPs will be recruited in the south of the Netherlands, contacted either directly or indirectly via various regional organisations by advisors of the regional supportive structures for primary care. GPs will be informed about the project, and when they agree to participate they will be instructed to send in an admission form with data on practice organization necessary for stratification and randomization.

Evidence of change will be assessed by studying the effects of the intervention on patients with CHF registered with the participating GPs. As in the pilot [10], GPs will include all CHF patients from their practices who are over 18 years of age of whom the GPs consider themselves to be the physician taking care of the treatment of this condition in the patient. We expect eight to ten patients per practice [18,19]. Patients will be sent explanation about the study and asked for informed consent to participate in a patient questionnaire. Data collection will be anonymized.

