### Time frame

Practice inclusion is planned from June until October 2010. After inclusion, practices participate in the programme during one year. At the start of the year, the GPs include all their patients with CHF they treat at least in part themselves. During that year, patients with newly diagnosed CHF can also be included. Data management in the patient registration forms is a continuous process during the project year. After the project period of a year, the forms are anonymised and sent to the researchers coded. Furthermore, practices will send coded patient questionnaires with explanation of the survey and ask for an informed consent; these will be returned to the researchers. Finally the researchers will contact the GPs participating for the telephone interview. The GPs will receive feedback based on the patient registration forms and the questionnaires.

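### The PACIC sample size counts included patients as returned questionnaires; with 60 practices, 80% power survives losses of only about 3% (8 included per practice) to 22% (10 included)

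*Protocol article*

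**What the plan says.** The Sample size section of the protocol article names the outcome: "Power calculations are based on the primary outcome measurement PACIC". The target is a difference of 0.3 points with a standard deviation of 1, "with alpha = 0.05 and beta = 0.20, ICC = 0.05". The result is "a total of 51 practices with 10 patients each would be required, or 59 practices with 8 patients".

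The Participants section sets recruitment: "The study population will consist of 60 general practitioners (GPs) and the CHF patients they will include". Of the patients whom GPs include it says "We expect eight to ten patients per practice", and it adds that consent is sought for the questionnaire.

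Under Time frame, GPs include their patients at the start of the year and may add new diagnoses during it. After the year, "practices will send coded patient questionnaires with explanation of the survey and ask for an informed consent", and the forms go back to the researchers. The Discussion confirms that the patient questionnaire is measured once, at the end. The Background says "Mortality in CHF patients is high compared to their age group" but gives no rate. The article states no expected return rate.

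**The concern.** The same figure, eight to ten, serves two purposes. Under Participants it is the number of patients a practice includes. Under Sample size it is the number of PACIC scores a practice contributes to the analysis. Between the two lie up to a year of follow-up, a consent request and a postal return. A patient lost at any of these steps yields no PACIC score, and there is no earlier PACIC measurement to fall back on.

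If losses exceed the small margin in the plan, power for the PACIC comparison is below the stated 80%. This matters because both arms receive an active programme, and the Discussion says that a smaller effect was targeted for that reason. A null result is therefore a realistic outcome. If it were read as coming from a trial with 80% power, it would count too heavily against tailoring.

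**Working it through.** **Inputs.** From Sample size: difference 0.3, SD 1, alpha 0.05, power 0.80, ICC 0.05. From Participants: 8 to 10 patients included per practice, and 60 GPs. Assumptions: two-sided test (this reproduces the stated figures), 1:1 allocation, 60 GPs meaning 60 practices, equal cluster sizes, and the return rates below.

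**Step 1: reproduce the stated figures.**

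Patients per arm without clustering = 2 × (1.96 + 0.8416)² / 0.3² = 174.4, so 348.8 in total.

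Design effect (DE) = 1 + (m − 1) × 0.05, and practices = 348.8 × DE / m.

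- m = 10: DE = 1.45; 348.8 × 1.45 / 10 = 50.6, rounded up to 51. Power with 51 × 10 is 80.3%.
- m = 8: DE = 1.35; 348.8 × 1.35 / 8 = 58.9, rounded up to 59. Power with 59 × 8 is 80.1%.

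Both counts are reproduced with no loss at all, so m must be the number of analysed PACIC scores.

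**Step 2: returns needed with 60 practices.**

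Solve 60m / (0.95 + 0.05m) = 348.8. This gives 42.56m = 331.4, so m = 7.79 returned per practice, or 60 × 7.79 ≈ 467 in total.

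Loss that can be absorbed = 1 − 7.79 / included:

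- 8 included: 2.7%
- 9 included: 13.5%
- 10 included: 22.1%

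**Step 3: power at assumed return rates, 60 practices.**

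Power = Φ(0.3 × √(60m / DE) / 2 − 1.96), with m = included × return rate. Example: 8 included at 80% return gives m = 6.4, DE = 1.27, 60 × 6.4 / 1.27 = 302.4, and Φ(0.3 × 17.39 / 2 − 1.96) = Φ(0.65) = 74%.

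| Return (assumed) | 8 included | 9 included | 10 included |
|---|---|---|---|
| 100% | 80.7% | 83.8% | 86.2% |
| 90% | 77.8% | 81.1% | 83.8% |
| 80% | 74.2% | 77.8% | 80.7% |
| 70% | 69.8% | 73.7% | 76.9% |
| 60% | 64.6% | 68.6% | 72.1% |

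**Step 4: difference detectable with 80% power, 60 practices.**

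Detectable difference = 2 × 2.8016 / √(60m / DE).

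- 8 included: 80% return, 5.603 / √302.4 = 0.32; 60% return (m = 4.8, DE = 1.19), 5.603 / √242.0 = 0.36.
- 10 included: 80% return (m = 8, DE = 1.35), 5.603 / √355.6 = 0.30; 60% return (m = 6, DE = 1.25), 5.603 / √288 = 0.33.

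**Sensitivity.** These are normal approximations. A t-based calculation with practices minus 2 degrees of freedom lowers power by about 1 to 2 points (60 × 8 at full return: 79.4%). Fewer than 60 practices would also lower it: 51 practices with 8 returns each give 74%.

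**The case against.** The strongest reply is that 60 practices already provide a margin. At 10 patients per practice the requirement is 51, which leaves nine spare practices, and a 20% loss still gives about 81% power. This stands. A reader might infer that any death, refusal or non-return takes the trial below 80%, and the figures do not support that. It is close to true only with 8 patients per practice, where 60 exceeds the requirement by one.

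Second, patients newly diagnosed during the year may be included and could replace some of those lost. This also stands as a possibility, but no number is given, so it cannot be relied on to cover the gap.

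Third, no return or mortality rate is documented, so the lower power figures are scenarios and not what the design is known to deliver. This is correct. The detectable differences at 60% to 80% return, 0.30 to 0.36, also remain below the 0.5 that the Discussion cites from earlier programme evaluations.

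Fourth, PACIC is one of several primary outcomes. A reader might take the shortfall to apply to the whole primary comparison. It does not: the guideline adherence index comes from registration forms completed by GPs and their staff, so questionnaire non-return does not reduce its data.

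Finally, stratification into solo, duo and group practices might suggest strongly unequal cluster sizes. The article gives no such distribution and expects a narrow eight to ten. An illustrative 1:2:3 ratio (coefficient of variation 0.41, an assumption) would cost about 2 points of power. That is worth at most a sensitivity figure.

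**Conclusion.** The point holds in a limited form. The stated calculation contains no arithmetic error. Its input is wrong in kind, because patients expected to be included are used as patients with a returned PACIC form. The trial therefore has 80% power for PACIC only while losses stay within about 3%, 13% or 22%, according to whether practices include 8, 9 or 10 patients. Over an assumed return of 60% to 80%, power runs from about 65% to 74% at the lower end of the expected range and from 72% to 81% at the upper end.

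This rests on 60 GPs meaning 60 practices, on equal cluster sizes, and on return rates that the article does not supply. The first assumption is favourable to the plan: practices are randomised, some with two or more GPs, so 60 GPs could mean fewer clusters. The documents do not show that power will fall short. They show that the stated 80% depends on an unstated and nearly complete return if practices have 8 patients each.

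**What to change.** State the requirement in returned PACIC questionnaires: about 467 in total over 60 practices, or 8 from each of 59. Say whether 60 GPs means 60 practices. Then give the power and the detectable difference for the planned number of practices over a stated range of return rates (for example 60% to 80%), recomputing the design effect at the reduced cluster size. A sensitivity figure for unequal cluster sizes is optional.

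Recruitment and design stay as planned, so the cost is a few restated figures. The drawback is a less favourable stated power for PACIC. No restatement is needed on this account for the guideline adherence index.

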### Time frame

Practice inclusion is planned from June until October 2010. After inclusion, practices participate in the programme during one year. At the start of the year, the GPs include all their patients with CHF they treat at least in part themselves. During that year, patients with newly diagnosed CHF can also be included. Data management in the patient registration forms is a continuous process during the project year. After the project period of a year, the forms are anonymised and sent to the researchers coded. Furthermore, practices will send coded patient questionnaires with explanation of the survey and ask for an informed consent; these will be returned to the researchers. Finally the researchers will contact the GPs participating for the telephone interview. The GPs will receive feedback based on the patient registration forms and the questionnaires.

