### Randomisation

The study will be a randomised controlled trial, with a one-year follow-up period. Practices are stratified according to practice size as solo, duo, or group practice. On inclusion, practices are assigned to one of the study groups using randomisation in blocks of four per stratum by a research assistant. Blocks were generated electronically with the help of a statistician. The randomising procedure itself is concealed for practices, consultants, and researchers ([name], MW). The regional advisors including the practices have no access to the randomisation process. After randomisation, both the practice and the regional advisor are informed. The intervention is open to all involved.

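### GPs appear to identify trial patients after their practice's allocation is disclosed, under an eligibility rule that rests on their own judgement and is worded in two ways, so the arms could differ in who is included

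*Protocol article*

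**What the plan says.** All references are to the protocol article.

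- **Allocation (Randomisation).** "On inclusion, practices are assigned to one of the study groups using randomisation in blocks of four per stratum by a research assistant". Then: "After randomisation, both the practice and the regional advisor are informed. The intervention is open to all involved".
- **Programme year (Time frame).** "After inclusion, practices participate in the programme during one year".
- **Patient inclusion (Time frame).** "At the start of the year, the GPs include all their patients with CHF they treat at least in part themselves". And: "During that year, patients with newly diagnosed CHF can also be included".
- **Eligibility (Participants).** GPs are to include all adult CHF patients "of whom the GPs consider themselves to be the physician taking care of the treatment of this condition in the patient".
- **Measurement (Measures, Discussion).** PACIC and EQ-5D are collected once, at the end, and the Discussion accepts that this leaves only comparisons between groups. Drug treatment at inclusion is recorded on the registration form.
- **Analysis (Data analysis).** The primary comparison is of outcomes at follow-up between arms, allowing for clustering.

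**The concern.** Randomising practices makes the arms comparable only if the set of patients in each practice is fixed without knowledge of the arm. Here the people who decide who is eligible appear to know the arm. The rule they apply depends on how they see their own role, and it has two wordings of different width. Treating a patient in part admits care shared with a specialist; regarding oneself as the physician in charge of the CHF treatment need not. Adding newly diagnosed patients is permitted, not required, so it may also be done to a different degree in each arm.

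If the tailored and standard practices draw the line differently, part of any difference in outcome reflects who was included and not what the programme did. Without a baseline PACIC or EQ-5D score, such a difference could be only partly seen and only partly corrected. The direction is unknown, so it could create a false difference or hide a real one.

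**Working it through.** **Order of events.** Set side by side, the sections give: practice joins; practice is allocated; practice is told; programme year begins; GPs include patients at its start; GPs may add new diagnoses during it. No sentence states outright that disclosure comes before the first patient is included, so that step is inferred. For patients added during the year no inference is needed. The concealment described under Randomisation protects the allocation of practices, not the later identification of patients.

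**The plan's own figure.** Inputs from Sample size: difference 0.3, SD 1.0, alpha 0.05 (two-sided reproduces the result), power 80%, ICC 0.05.

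- Per arm without clustering: 2 × (1.96 + 0.8416)² / 0.3² = 174.4.
- 10 patients per practice: design effect 1 + 9 × 0.05 = 1.45; 2 × 174.4 × 1.45 / 10 = 50.6, so 51 practices.
- 8 patients per practice: design effect 1 + 7 × 0.05 = 1.35; 2 × 174.4 × 1.35 / 8 = 58.9, so 59 practices.

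Both stated figures are reproduced. They presuppose comparable patients in the two arms.

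**Precision with 60 practices, 30 per arm.** SE = √(2 × design effect / (30 × m)), where m is patients per practice.

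- m = 8: √(2 × 1.35 / 240) = 0.106.
- m = 10: √(2 × 1.45 / 300) = 0.098.

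**Effect of differential inclusion.** Suppose there is no true effect, and a share f of one arm's patients would not have been included in the other arm. If their mean PACIC differs by d points, the bias is b = f × d. The rejection rate is P(|Z + b/SE| > 1.96). Both f and d are assumptions; the documents give neither.

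| f | d | b | b / 0.3 | Type I error, m = 8 | Type I error, m = 10 |
|---|---|---|---|---|---|
| 10% | 0.3 | 0.03 | 10% | 5.9% | 6.1% |
| 10% | 0.5 | 0.05 | 17% | 7.6% | 8.0% |
| 20% | 0.5 | 0.10 | 33% | 15.6% | 17.4% |
| 30% | 0.5 | 0.15 | 50% | 29.3% | 33.2% |

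In a practice of 8 patients, 10%, 20% and 30% are 0.8, 1.6 and 2.4 patients. The upper value of d equals the PACIC difference that the Discussion cites from evaluations of a CHF and a diabetes programme, so it is a demanding assumption for patients at the margin of eligibility.

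The bias can also work against a real effect. With m = 8, a bias of 0.10 opposing a true difference of 0.3 leaves 0.20, and 0.20 / 0.106 = 1.89. Power then falls from 81% to about 47%.

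**The case against.** Several points on the other side are sound.

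- **GPs are not asked to choose.** A reader might infer that they hand-pick patients once they know the arm. Both sections tell them to include every eligible patient, so discretion lies only at the edge of eligibility and in the optional new diagnoses.
- **Both arms are active.** The materials, registration form and number of visits are the same; what differs is how the visit agenda is set. A loose rule applied equally in both arms does not bias the comparison. The tailored arm does review barriers such as complex patients and lack of staff (Table 2), and each included patient adds paperwork, so a difference is plausible. It is not shown.
- **The primary outcomes are not equally exposed.** For the GAI, treatment at inclusion is recorded and could be adjusted for. For PACIC and EQ-5D, it would be too strong to say that imbalance cannot be detected: the form records demographics, aetiology, diagnostic basis and type of CHF (Standardised delivery of the implementation programme). These can show some imbalance in case mix, but they do not replace a baseline score.
- **Follow-up is not contradicted.** A reader might infer that adding patients during the year conflicts with the one-year follow-up. That year can be read as the practice's time in the programme, and the documents do not give the share of late entries.

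One might also say that the full protocol could contain a patient list made beforehand. But the article states when patients are included, so the concern comes from the described design and not from a missing detail.

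**Conclusion.** The concern holds as a risk of identification bias. The two eligibility wordings differ and must be reconciled, and on the plain reading patients are identified after disclosure. The risk is greatest for PACIC and EQ-5D and smaller for the GAI.

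Its size cannot be derived from the documents. On the assumed values, a bias of 0.03 to 0.15 PACIC points gives a two-sided type I error of about 6% to 29% with 8 patients per practice (6% to 33% with 10). A figure near 15% is one assumed point in that range and should not be quoted as the trial's error rate. The documents do not support saying that the arms will differ, or that all three primary outcomes are equally at risk. The matter still deserves correction before practices are allocated, because the target difference is only 0.3 and analysis cannot fully repair the two questionnaire outcomes.

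**What to change.** 1. Replace the wordings under Participants and Time frame with one eligibility sentence that settles whether shared care qualifies.
2. Have each practice send a coded list of all eligible CHF patients with the admission form that it already submits, and release its allocation only once the list has been received.
3. Make the listed patients the primary analysis set.
4. Report patients diagnosed during the year separately, outside the primary comparison.
5. Report by arm the numbers eligible and included, and their recorded characteristics.

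**Cost.** Each practice must find its cases before allocation, about 8 to 10 patients on the protocol's expectation. This adds to an administrative load that the Discussion already acknowledges. Allocation is slightly delayed, and some newly diagnosed patients leave the primary set. The required number of practices and the intervention do not change.

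**Practices already allocated.** A list drawn up after allocation does not remove the bias. Use it only for a sensitivity analysis and state the limitation in the report.

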The paper template is used to direct care and collect data to demonstrate the effectiveness of the interventions. Demographic data is collected in particular the aetiology of the CHF and the diagnostic category, whether diagnosis was echocardiography based, on the existence of diastolic or systolic CHF, and pharmaceutical treatment at the start of the project period. A second page poses questions about non-pharmaceutical issues such as advice about physical activity and influenza vaccination. Finally, we offer different forms for patients with systolic or diastolic CHF, based on the recommendations on medication as summarised in Table 1.

The pilot study demonstrated that three practice visits was the optimum number and these shall be offered to all participating practices. The practice visitor is an educational facilitator trained in supporting behaviour change in practices.

The pilot study also demonstrated that there was little multidisciplinary clinical activity in the improvement of care for CHF patients, and this has been addressed in this project. We now use the multidisciplinary practice guideline as a starting point instead of the monodisciplinary GP's practice guideline. Furthermore, the regional advisors will determine the social network in the practice area, providing information on other primary care disciplines, *e.g*., dieticians and physiotherapists, with extra expertise and interest in CHF treatment. These workers in the other disciplines will be informed about the project and receive relevant information in line with the multidisciplinary guideline.

All materials are offered paper based in a binder. We will also present all materials on a website and examine the possibilities for designing the guiding patient registration forms on this website as well.

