### Measures

Data collection will comprise the following measures: patient questionnaires, patient registration forms, and telephone interviews with the GPs. Practices will send out patient questionnaires based on validated and previous used questionnaires: PACIC [21], EQ-5D [22], questions about 'continuity of care,' and Morisky's questionnaire on medication adherence [23]. In the patient registration forms, data about non-pharmaceutical and drug therapy are registered by the GPs and their staff: they register the baseline treatment at inclusion, and during the patient contacts throughout the study period they register all advice given, referrals, drug therapy changes, and information on hospitalisation and mortality. The GP interview will score goal attainment and a qualitative assessment of the programme. All measures have been applied by our group in previous studies.

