### Data analysis

The primary analysis is a comparison of primary outcomes at follow-up between the study groups, taking into account clustering of patients within practices. Multilevel regression analyses will be used to explore the effect of practice size and type of intervention programme. In addition, we will examine both changes within groups and differences at follow-up between groups with respect to percentage of patients on the maximum tolerated dosage of ACE inhibitor or angiotensin II receptor blocker and of beta blockage; medication completely according to the guideline; having received influenza vaccination in the winter season 2010-2011; having received professionally guided physical activity training; and the number of non-pharmaceutical issues addressed. If possible, subgroup analyses will comprise type of CHF (systolic or diastolic) and diagnostic certainty (secondary care diagnosis, echocardiography diagnosis) The interviews will be used to assess the feasibility of the programme and goal attainment, organisational changes in CHF care, and formalised cooperation with other primary care disciplines and specialist care.

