## Discussion

There exist various classifications of barriers (and facilitators) and multiple approaches for linking interventions to barriers [29-31]. In their systematic review, Légaré and colleagues propose a conceptual framework with knowledge, attitude, and behaviour as main factors [31]. Our choice of barriers is based on a list rigorously developed in the Netherlands with a literature study in 2002, expert input, and tested in various projects in the Netherlands [20]. Our main factors for ordering the barriers are related to the innovation, the healthcare professional, the patient, and the context. The barriers presented in this study correspond very well to the barriers found most often in the Légaré review, including time pressure and lack of applicability. Looking for the barriers for each individual practice and not for the practices participating in general, we decided to have the barriers proposed scored in email contact with the GPs in two rounds.

Several studies were conducted to assess the effect of tailoring implementation. In a systematic review, the authors conclude that identifying barriers and tailoring intervention to these barriers may improve clinical practice compared to no intervention and to guideline dissemination. In their meta analysis including eight studies identified with a non-tailored intervention in the control group, they report a modest effect of tailoring [13].

All data collection will take place at the end of the project period. Within the context of the evaluation of the implementation project, it is not feasible to have data collection both at the start and at the end, but the patient registration form will have baseline data on treatment issues. This also will allow for within group analyses, giving information about the effectiveness of both implementation strategies separately. Unfortunately, this data collection, either paper based or electronically, will require additional administrative actions from the practices. Enabling data collection from the electronic medical record will be beyond the scope of this project. Considering the patient questionnaire's results, with one measurement at the end, this restricts us to intergroup analyses.

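### Patients newly diagnosed during the project year are observed for almost 0 to 12 months, so the planned within-group changes mix first treatment and short observation with programme effect

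*Protocol article*

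**What the plan says.** All references are to the protocol article.

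- **Entry (Time frame).** The practice's period is fixed: "After inclusion, practices participate in the programme during one year". For known patients: "At the start of the year, the GPs include all their patients with CHF they treat at least in part themselves". For new cases: "During that year, patients with newly diagnosed CHF can also be included". No cut-off date and no minimum time in the programme is given.
- **Assessment (Time frame, Discussion).** Registration forms are returned and patient questionnaires are sent out once the practice's year is over. The Discussion confirms this: "All data collection will take place at the end of the project period". The exception is the treatment baseline held on the registration form.
- **Follow-up (Randomisation).** "The study will be a randomised controlled trial, with a one-year follow-up period".
- **Baseline.** The section on standardised delivery lists, among the contents of the form, "pharmaceutical treatment at the start of the project period". Measures says of GPs and their staff that "they register the baseline treatment at inclusion".
- **Analysis (Data analysis, Discussion).** The primary analysis compares the arms at follow-up and allows for clustering. Changes within groups are also planned for a list of prescribing and advice measures, among them "the number of non-pharmaceutical issues addressed". The Discussion says the baseline data on the form make it possible to learn how well each strategy works separately. The patient questionnaire is given once, so PACIC and EQ-5D allow only between-arm comparisons.

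**The concern.** The date of assessment belongs to the practice, while the date of entry belongs to the patient. For patients listed at the start these are about a year apart. For a patient diagnosed in month 11 they are about one month apart.

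A before-after change is meant to show what a year of the programme did to the care of patients under treatment. A newly diagnosed patient's baseline lies at or near diagnosis. Moving from little or no heart failure medication to guideline medication is then largely the consequence of being diagnosed. Pooling such patients with the others credits the programme with that step. Short observation works the other way on measures that accumulate over contacts, such as issues addressed. At stake is what the trial may say about each delivery mode on its own, where no untreated control group exists to remove the error.

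**Working it through.** **1. Timing.** Start-of-year patients have about 12 months between inclusion and assessment. New cases have from almost 0 to almost 12 months. This follows from the text alone.

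**2. Within-group change.** Let p be the share of new cases, D_s the change in start-of-year patients, and D_n = u + e the change in new cases. Here u is what would follow diagnosis anyway and e is the programme's part. The observed change is

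D = (1 − p)·D_s + p·(u + e).

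The term p·u is not programme effect. It equals 0.1u, 0.2u or 0.3u for p = 10%, 20% or 30%. The documents give neither p nor u, so no figure can be put on it. For prescribing measures u is plausibly positive, and smaller if the form is filled in after the first prescription.

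**3. Accumulating counts.** Assume even arrival over the year (mean observation 6 of 12 months) and a constant rate of issues addressed. The group mean is then multiplied by 1 − p/2, that is 0.95, 0.90 or 0.85. This is illustrative, since a new diagnosis may bring more contacts early on.

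**4. The plan's sample size.** Inputs from Sample size: difference 0.3, SD 1, alpha 0.05 (taken as two-sided), power 80%, ICC 0.05.

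- Per arm without clustering: 2 × ((1.960 + 0.842)/0.3)² = 174.4.
- 10 patients: design effect 1 + 9 × 0.05 = 1.45; 2 × 174.4 × 1.45/10 = 50.6, so 51 practices.
- 8 patients: design effect 1 + 7 × 0.05 = 1.35; 2 × 174.4 × 1.35/8 = 58.9, so 59 practices.

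Both stated figures reproduce. Power is 80.3% and 80.1%.

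**5. Possible dilution of PACIC.** If new cases lose a fraction L of the effect, the mean difference is 0.3 × (1 − pL). With 59 × 8 the effective number per arm is 59 × 8/2/1.35 = 174.8, and power is Φ(difference × √(174.8/2) − 1.96). The shares are assumed.

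| Share p | L = 0 | L = 0.5: difference, power | L = 1: power |
|---|---|---|---|
| 5% | 80.1% | 0.293, 78.1% | 75.9% |
| 10% | 80.1% | 0.285, 75.9% | 71.4% |
| 20% | 80.1% | 0.270, 71.4% | 61.2% |
| 30% | 80.1% | 0.255, 66.4% | 50.1% |

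If new cases come on top of the eight, so that m = 8/(1 − p), and L = 0.5, power is 78.9%, 77.7% or 76.6% for p = 10%, 20% or 30%.

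**6. Would leaving them out help the primary comparison?** Dropping new cases from the eight leaves m = 8(1 − p) and the full 0.3. Power is then 77.1%, 73.5% or 69.1% for p = 10%, 20% or 30%, against 75.9%, 71.4% or 66.4% when they are kept with L = 0.5. The two options break even where 1 − pL = √[(1 − p) × 1.35/(1 + (8(1 − p) − 1) × 0.05)]:

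- p = 10%: √(0.9 × 1.35/1.31) = 0.963, so L = 37%
- p = 20%: √(0.8 × 1.35/1.27) = 0.922, so L = 39%
- p = 30%: √(0.7 × 1.35/1.23) = 0.877, so L = 41%

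Below these losses, exclusion costs power.

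**The case against.** The practice is randomised, receives the visits and takes part for one year. A reader might infer that open entry contradicts the stated one-year follow-up. It does not: the statement describes the trial and is true of the practice, and nothing promises each patient 12 months.

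A reader might also infer that the two descriptions of baseline cannot both hold. The first describes what the form contains and the second gives the working rule, baseline at inclusion. They coincide for start-of-year patients, and the second covers new cases.

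The strongest inference would be that new cases dilute all three primary outcomes and should leave the primary analysis. That requires the effect to grow with the patient's own time in the study. The programme acts on GPs and practice organisation, so a late entrant may meet a practice that has already changed, and then nothing is lost. Dilution is plausible for PACIC, which asks about care received. For EQ-5D and the guideline adherence index the documents support neither direction nor size. Inclusion of new cases is optional and may be rare. The entry rule is the same in both arms, so it creates no between-arm bias by itself. Including every patient the practice treats is also a legitimate target population for an implementation trial, and analysis sets are often left to the analysis plan.

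All of this stands for the between-arm comparison. It does not answer the within-group point. There, baseline at inclusion is exactly what puts a new patient's starting point around diagnosis, and no second arm enters the calculation to cancel the resulting change.

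**Conclusion.** The point holds for the within-group analyses. Followed as written, they combine patients with about a year of observation and patients with anything down to almost none, whose change partly reflects diagnosis. The error is p·u, proportional to an unstated share of new cases, and it concerns the analyses meant to judge each strategy separately. Restricting them to start-of-year patients removes this component only; they remain uncontrolled before-after comparisons.

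For the between-arm PACIC comparison, dilution is possible but not shown. On 59 × 8, power ranges from 80% with no loss to about 76% or 71% if 10% or 20% are new cases who lose half the effect. These shares and losses are assumptions. Removing new cases from the primary analysis would be a trade-off, helpful only above a loss of about 37% to 41%, so the documents justify a sensitivity analysis and not a change of the primary population.

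**What to change.** 1. In Data analysis, limit change-from-baseline analyses to patients included at the start of the practice's project year.
2. Report newly diagnosed patients separately, by months since inclusion, with baseline at their own inclusion as Measures already provides.
3. In Randomisation or Time frame, state that the one-year follow-up is the practice's and that patient observation is shorter for new cases.
4. Prespecify a repeat of the between-arm primary comparison in start-of-year patients as a sensitivity analysis, keeping the primary population as it is.

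The cost is a few sentences and somewhat fewer patients in the within-group analyses. The date of inclusion must be on the registration form, which the article does not confirm. No other new data are needed.
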